### Data analysis

#### Qualitative data analysis

The content analysis method will be used, which is an appropriate approach to the analysis and categorization of qualitative data according to empirical and theoretical criteria [35]. Data from the discussion groups and diaries will be transcribed literally. After verification of the authenticity of the transcriptions, the text will be fragmented in descriptive codes assigned on the basis of its content. In a second stage of the analysis, these codes will be grouped into interpretative categories, bearing in mind their similarities and differences and relating them to the main themes identified in the theoretical framework and the study objectives. This process is not linear or sequential but is rather constant, cyclic, recursive and complex, demanding the construction of data for their subsequent reconstruction and interpretation of their meaning [35, 36]. The NVivo platform, version, 10 will be used in the analysis.

#### Quantitative data analysis

The analysis will focus on numerical differences, obtained in the WAI-S and IRI, observed before and after the group phases of the PAR. Descriptive statistics will be used for sample description and evaluation of the scores. Differences between baseline scores and the post-group assessment will be estimated through the application of a parametric test (Student’s *t*-test for paired data) in the case of quantitative variables after confirmation of the normality and homogeneity of their variance; for data that do not follow a normal distribution), non-parametric tests will be used: the Wilcoxon test will be used for quantitative variables and the chi-square test or Fisher’s exact test for qualitative variables. To interpret the results, statistical significance will be set at *p* < 0.05 for a 95% confidence interval (95% CI) in the case of a bidirectional hypothesis. The analysis will be performed with the IBM SPSS Statistics 21 package.

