**Methods/Design:**

The study will use a mixed method design. Qualitative methodology, through participative action research, will be employed to implement scientific evidence on the therapeutic relationship. A quasi-experimental, one-group, pre-test/post-test design will also be used to quantitatively measure the effectiveness of the implementation of the evidence. Participants will consist of nurses and patients from two psychiatric units in Barcelona. Nurses will be selected by theoretical sampling, and patients assigned to each nurses will be selected by consecutive sampling. Qualitative data will be gathered through discussion groups and field diaries. Quantitative data will be collected through the Working Alliance Inventory and the Interpersonal Reactivity Index. Qualitative data will be analysed through the technique of content analysis and quantitative data through descriptive and inferential statistics.

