### Objectives

General:To generate change in how nurses establish the therapeutic relationship in an acute psychiatric unit, based on PAR.To evaluate the effectiveness of the implementation of scientific evidence through PAR, in terms of improving the therapeutic relationship, as perceived by nurses and patients, and enhancing empathy, as perceived by nurses.

Specific:To describe how nurses in an acute psychiatric unit perceive the establishment of the therapeutic relationship with patients.To identify nursing professionals’ difficulties and limitations when establishing a therapeutic relationship with a patient.To identify the elements of change and improvement in the establishment of the therapeutic relationship, based on contrasting the evidence with real-world clinical practice.To qualitatively evaluate the effects of the implementation of evidence on the development of the therapeutic relationship between nurses and patients.To analyse the impact of the implementation of scientific evidence on the establishment of the therapeutic relationship on:Measurement of the therapeutic relationship, evaluated by staff before and after the PAR process.Measurement of the therapeutic relationship, evaluated by patients before and after the PAR process.Measurement of empathy, evaluated by staff before and after the PAR process.

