### Setting and participants

The study will be conducted in the acute psychiatric admissions ward of the Institute of Neuropsychiatry and Addictions (*Institut de Neuropsiquiatria i Addiccions* [INAD]) of Parc de Salut Mar de Barcelona (Spain): the Institute consists of 4 units with 107 in-patient beds for patients with acute psychiatric disorders. These units cover a population of approximately 650,000 inhabitants in the City of Barcelona, Badalona and Santa Coloma de Gramanet.

Study participants will consists of nurses working in the acute-stay units and patients admitted to these units. Theoretical sampling will be carried out in nurses. The sample will be composed of 9–10 participants representing the distinct socio-occupational profiles in the units. Thus, the group will be composed of nurses from each of the three shifts, by specialist and generalist nurses, and by staff and supply nurses. The aim is to guarantee the principles of heterogeneity and accessibility [28].

We estimate that about 30 patients will be allocated to each participating nurse in the phase prior to the start of the groups, and consequently, accepting an alpha risk of 0.05 and a beta risk of 0.2 in the bilateral contrast, nine participants will be needed to detect a difference equal to or higher than 10 units in the Working Alliance Inventory-Short (WAI-S). A standard deviation of 10 will be accepted, and a loss to follow-up rate of 10%. Consecutive sampling will be performed. Inclusion criteria will consist of the following: a) Being assigned to a participating nurse, b) Having established a link with the participating nurse during a hospital stay longer than 3 days, b) voluntarily accepting to participate in the project and providing signed informed consent.

Exclusion criteria will consist of a) showing signs of the initial stages of psychomotor agitation, and b) being subjected to physical restraint, either currently or within the last 24 h.

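### The paired t-test for the WAI-S has no stated unit: the sample size points to nurses, but the scores come from about 30 patients per nurse who are probably not measured twice

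*Protocol article*

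**What the plan says.** All references are to the protocol article.

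- **Test.** Under Quantitative data analysis, "Differences between baseline scores and the post-group assessment will be estimated through the application of a parametric test". The test named is Student's t for paired data, with Wilcoxon if normality fails. It covers the WAI-S and the IRI together. No unit of analysis and no nurse term is given.
- **Patients.** The abstract says that "patients assigned to each nurses will be selected by consecutive sampling". Setting and participants adds that "about 30 patients will be allocated to each participating nurse in the phase prior to the start of the groups", and requires an inpatient stay of more than 3 days. No post-phase number is given.
- **Nurses.** "The sample will be composed of 9–10 participants representing the distinct socio-occupational profiles in the units".
- **Patient-rated outcome.** One specific objective is "Measurement of the therapeutic relationship, evaluated by patients before and after the PAR process". The article does not say whether the same patients are meant at both times.
- **Sample size.** At a two-sided alpha of 0.05 and 80% power, "nine participants will be needed to detect a difference equal to or higher than 10 units in the Working Alliance Inventory-Short (WAI-S"), with an SD of 10 and 10% loss to follow-up.

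**The concern.** A paired test needs a unit that is measured twice. The nurses are such a unit, and the IRI fits directly because it gives one value per nurse per phase. The patient-rated WAI-S comes from acute inpatients recruited one after another before the groups start. The second measurement follows the group phase, which has four sessions, and re-measuring the first patients is not planned anywhere. If the later patients are new, there is nothing to pair at patient level. The nurse-rated WAI-S has the same structure if the nurse completes one form per patient, which the article does not settle.

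An analyst holding some 270 forms per phase could pool them, either unpaired or matched in an arbitrary order. That treats the forms as independent although they come from about nine nurses. The standard error, and with it the p-value and confidence interval for two of the three dependent variables, could then be wrong. The section also makes the paired t-test conditional on homogeneity of variance, which belongs to independent samples. This is a further sign that the unit was not settled.

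**Working it through.** **1. The plan's own figure.** Inputs from Setting and participants: two-sided alpha 0.05, power 0.80, difference 10, SD 10, loss 10%.

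- Paired normal formula: n = ((1.960 + 0.842) × 10/10)² = 7.85, rounded up to 8. After loss, 8/0.9 = 8.9, rounded up to 9. The stated nine is reproduced.
- Exact paired t: 10, and 10/0.9 = 11.1, so 12 after loss.
- Two independent groups: 2 × 7.85 = 15.7, so 16 per phase, and 18 after loss.

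Of these, only the paired normal version gives nine. It takes SD 10 as the SD of a paired change on about nine units.

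**2. Units against rows.** Nine to ten nurses with about 30 patients each give 9 × 30 = 270 to 10 × 30 = 300 nurse-patient ratings before the groups. The sizing therefore fits the 9–10 nurses and does not fit the rows of WAI-S data.

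**3. Effect of ignoring the nurse.** Assumptions, because the article gives none of these: J = 9 nurses, m = 30 different patients per nurse in each phase, total score variance σ² = 100, between-nurse share ICC, and a fraction f of the nurse variance that is specific to the phase (so nurse effects correlate 1 − f between phases).

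- True variance of the mean change: 2σ²·ICC·f/J + 2σ²(1 − ICC)/(Jm).
- Naive variance, unpaired: 2σ²/(Jm).
- Ratio of the two: 1 + ICC(mf − 1).

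Worked case, ICC 0.10 and f 0.5:

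- True SE = √(10/9 + 180/270) = √1.778 = 1.333.
- Naive SE = √(200/270) = 0.861.
- SE ratio = 1.55, or √(1 + 0.10 × 14) = √2.4.
- Approximate type I error = 2[1 − Φ(1.96/1.55)] ≈ 21%.

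**4. Simulation with no true change**, 20,000 trials per setting, nominal 5%. Row-paired means that patients of the same nurse are matched arbitrarily.

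| ICC | f | SE ratio | Unpaired patients | Row-paired patients | Paired nurse means |
|---|---|---|---|---|---|
| 0.05 | 0 | 0.97 | 4.6% | 5.2% | 5.2% |
| 0.10 | 0 | 0.95 | 4.1% | 5.0% | 4.9% |
| 0.10 | 0.1 | 1.10 | 7.5% | 8.8% | 4.7% |
| 0.05 | 0.2 | 1.12 | 8.1% | 8.6% | 4.9% |
| 0.10 | 0.2 | 1.22 | 10.9% | 12.3% | 4.9% |
| 0.05 | 0.5 | 1.30 | 13.3% | 13.6% | 4.9% |
| 0.10 | 0.5 | 1.55 | 20.9% | 21.8% | 4.9% |
| 0.20 | 0.5 | 1.95 | 32.4% | 34.5% | 5.2% |

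A separate run of 3,000 trials per setting agreed. It gave 7–8% at ICC 0.05 with f 0.2 and 31–33% at ICC 0.20 with f 0.5. With f = 0 the unpaired test gave 2.8–4.5%. Nurse means stayed at 4.3–5.3%.

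**The case against.** The strongest reply is that the planned test is sound as it stands. The article names a paired t-test, never says that patient rows are to be paired, and sizes the study at nine, which points to nurses. On nurse means both WAI-S versions can be analysed with exactly that test, and it holds its level. This stands in part: the paired t-test is not wrong in itself, and a reader should not infer that the WAI-S cannot be analysed with it. What is missing is the instruction to average by nurse. The sizing paragraph does not supply it, since the abstract uses participants for nurses and patients alike.

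Three stronger readings are tempting, and the article does not support them.

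- **That the post-phase patients are proven to be different people.** The article never says so. Setting 270–300 ratings against the Institute's 107 beds does not prove it either. With nurses from three shifts, one patient may rate several nurses; if each rated three (an assumption), these would be 90–100 people. Different patients are very likely on an acute ward, but this is an inference.
- **That any patient-level analysis is invalid.** A mixed model on patient rows with nurse and nurse-by-phase effects is valid.
- **That the usual design effect 1 + 29 × ICC (2.45 to 6.8 for ICC 0.05 to 0.20) applies.** The same nurses serve both phases, so stable nurse differences cancel. That factor is reached only when f = 1.

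It can also be said that a condensed article leaves modelling detail to a fuller document, and that the quantitative part only complements a qualitative study. The first point would excuse silence. Here, however, a specific test is fixed for data that, row by row, probably cannot be paired. The second limits the weight of the finding but does not remove it.

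**Conclusion.** The concern holds as a mismatch between the unit that the sample size implies (the nurse) and the rows on which the WAI-S is collected (patients within nurse), with no statement of which one the paired test uses. At patient level the test is probably impossible to run as a true paired test. A pooled substitute that ignores the nurse has type I error of about 5% or less if nurse effects are stable between phases. It has about 7 to 35% for ICC 0.05 to 0.20 with 20 to 50% of nurse variance phase-specific.

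Those shares, the 30 patients per nurse in the post phase and the total SD of 10 are assumptions. Some phase-specific variation is plausible, because the intervention aims to change how nurses relate to patients and they may change unequally. The paired t-test on nurse means holds about 5% in every setting tried. The IRI is not affected.

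**What to change.** - State whether the post-phase patients are new or the same people, and how many are expected per nurse.
- Name the nurse as the unit of inference for the WAI-S.
- For both WAI-S versions, run the paired t-test on each nurse's pre-phase and post-phase mean. Alternatively, fit a linear mixed model with phase as fixed effect, nurse and nurse-by-phase random effects, and Kenward-Roger or Satterthwaite degrees of freedom. Add a patient random effect where a patient rates more than one nurse or is measured twice.
- Keep the simple paired test for the IRI.
- Record nurse and phase identifiers on every form.

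The cost is a change of wording and two identifiers per form; no further data are needed. The p-value may be less favourable than from a pooled patient-level test, because inference then rests on about nine nurses.

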**Fig 2 Fig2:**
[figure not shown]
Study design

Therefore, to achieve the first objective, a qualitative design will be used in the form of PAR, within the constructivist paradigm and following the model of Kemmis and McTaggart [24] in cycles and stages. PAR is a method that integrates research and social action [25] and, during its implementation, includes the following stages: a) analysis of the situation, b) identification of problems and design of strategies for the proposed action, c) implementation of the strategies designed, and d) observation and systematic reflection on their implementation.

To achieve the second objective, a quasi-experimental study of a single pre-test/post-test group is proposed, with evaluation of the implementation of the evidence through PAR [27].

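### The paired t-test is made conditional on equal variances, which it does not need, and on normality of the variables rather than of the paired differences

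*Protocol article*

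**What the plan says.** In the protocol article, Methods/Design, Quantitative data analysis, before/after differences in WAI-S and IRI are to be tested with Student's t-test for paired data "after confirmation of the normality and homogeneity of their variance". "Their" refers to the quantitative variables; the paired differences are not mentioned. Data that are not normal go to the Wilcoxon test. Nothing is said about what happens if normality holds and homogeneity does not, and no test or threshold is named for either check.

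Under Study design, "a quasi-experimental study of a single pre-test/post-test group is proposed", so there is no second group whose variance could be compared. Under Setting and participants, "The sample will be composed of 9–10 participants" describes the nurse sample. The size calculation there states "accepting an alpha risk of 0.05 and a beta risk of 0.2 in the bilateral contrast", that "nine participants will be needed to detect a difference equal to or higher than 10 units" on the WAI-S, and "A standard deviation of 10 will be accepted, and a loss to follow-up rate of 10" per cent.

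**The concern.** Homogeneity of variance is an assumption of the two-sample t-test. In a paired design the test is a one-sample test on differences, and the before and after variances enter only through the variance of the difference. The stated condition is therefore not an assumption of the test it guards. Normality of the separate before and after scores is also not what the test needs.

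A change in spread is a plausible result of an intervention meant to change how nurses work, for example if the lower-scoring nurses move up more. Under the rule as written, that change would count against a test that is still valid. The analyst would then have no stated route: the t-test is barred, and Wilcoxon is offered only for non-normal data. The choice would be made after seeing the data, and with it whether a mean difference and confidence interval are reported.

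**Working it through.** **1. The plan's own figure.** Inputs from Setting and participants: two-sided alpha 0.05, power 0.80, difference 10, SD 10, loss 10%. Taking the SD as that of the paired differences:

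n = [SD × (z₀.₉₇₅ + z₀.₈₀) / difference]² = [10 × (1.960 + 0.842) / 10]² = 7.85, rounded up to 8; 8 / 0.9 = 8.9, rounded up to 9.

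The stated nine is reproduced by a paired, normal-theory calculation. Removing the conditions on the test leaves it unchanged.

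**2. Does the paired t-test need equal variances?** With D = after − before,

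t = mean(D) / (s_D / √n), on n − 1 degrees of freedom, and Var(D) = σ₁² + σ₂² − 2ρσ₁σ₂.

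Nothing requires σ₁ = σ₂. Simulation at n = 9 with normal scores, assumed correlation 0.5 and no true difference (200,000 runs for the t-test, 20,000 for a median-centred Levene test):

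| SD before / after | Type I error, paired t | Levene rejects |
|---|---|---|
| 10 / 10 | 0.050 | 1% |
| 10 / 20 | 0.051 | 20% |
| 10 / 30 | 0.050 | 52% |
| 20 / 10 | 0.050 | 20% |

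The t-test keeps its level throughout, while a homogeneity check would often fail.

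**3. Cost of the normality check alone.** At n = 9, normal differences, effect of one SD, Shapiro-Wilk at 0.05 deciding between t and exact Wilcoxon: power is 0.739 for t throughout and 0.736 for the gated rule (20,000 runs). The loss is 0.739 − 0.736 = 0.003, or 0.3 points. (Exact power of the paired t-test at n = 9 is 0.748.)

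**4. Cost if failed homogeneity also sends the analysis to Wilcoxon.** The article does not state this route; it is the natural reading if the t-test is barred. Setting: n = 9, correlation 0.5, true difference 10, Wilcoxon used if either Shapiro-Wilk or Levene rejects.

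- SD falls from 10 to 5: Var(D) = 100 + 25 − 50 = 75, SD of D = 8.66. Power is 0.856 for t and 0.824 gated with a mean-centred Levene test, a loss of 3.2 points. A separate run gave 0.853 and 0.836, a loss of 1.7 points.
- SD falls from 10 to 3.33: Var(D) = 100 + 11.1 − 33.3 = 77.8, SD of D = 8.82. Power is 0.841 for t, against 0.793 gated (mean-centred Levene) or 0.801 (median-centred), a loss of 4.8 or 4.0 points (10,000 runs).

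The cost is thus about 2 to 5 points for a two- to three-fold fall in SD.

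**The case against.** The strongest reply is that the rule does little harm. At n = 9 a normality check seldom rejects when the data are near normal, so the t-test is used almost always. Where the differences are skewed, the check even helps a little: type I error is 0.102 for the ungated t-test against 0.096 gated (exponential differences), and 0.080 against 0.077 (chi-square with 4 degrees of freedom). Under the symmetric distributions tried, the gated error stays at 0.047 to 0.051. The article also names no formal test, so inspecting plots could count as confirmation. The written switch to Wilcoxon mentions only non-normality. The quantitative part complements a mainly qualitative study.

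All of this stands as to size, and it rules out claiming that dropping the checks improves error control. It does not rescue the homogeneity condition, which is wrong whatever check is used, nor does it fill the missing branch. An unseen analysis plan might add detail, but the rule printed here would still need correcting.

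Three stronger readings are tempting and not supported:

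- A reader might infer a power loss of about 6 points at n = 9 (0.739 to 0.677). That compares always using t with always using Wilcoxon; the article plans neither.
- A reader might infer that a normality check at n = 9 almost never detects anything. Shapiro-Wilk rejects 39% of the time for exponential and 22% for lognormal (0.5) differences. It usually misses such departures, which is a weaker statement.
- A reader might infer that with about 30 patients per nurse (9 × 30 = 270 ratings) the check would reject for trivial truncation at the scale maximum. For raw scores capped at 84 with SD 10, rejection runs from 7% at a mean of 55 to 100% at a mean of 70, and the article gives no mean. It also presumes that patient ratings are the unit of analysis, which is a separate matter.

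**Conclusion.** The point holds as a correction to a stated rule, with modest consequences. Homogeneity of variance is not a condition of the paired t-test in this one-group design, the normality condition is attached to the wrong quantity, and the route is undefined when homogeneity alone fails. The first two follow from the form of the test and the third from the text; none depends on simulation.

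The size does rest on assumptions: Shapiro-Wilk and Levene at 0.05, nine complete pairs, normal scores and correlation 0.5. On these, the normality check costs about 0.3 points of power, and routing failed homogeneity to Wilcoxon about 2 to 5 points when the SD falls two- to three-fold. The stated sample size is not affected. The case for the change is that it removes an error and a data-driven choice at almost no cost, not that the present rule would seriously mislead.

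**What to change.** In Quantitative data analysis:

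- Delete the homogeneity-of-variance condition.
- State that the distributional assumption concerns the paired differences.
- Name the paired t analysis in advance as the main analysis for WAI-S and IRI, reported as a mean difference with 95% CI whatever the checks show.
- Report the Wilcoxon signed-rank test on the same differences as a stated sensitivity analysis. This also covers marked skewness, where the ungated t-test can run slightly above its nominal level.

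The cost is a change of wording and one extra line of results per outcome. The change leaves open the unit of analysis for patient-rated WAI-S, which has to be settled separately.

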### Ethical considerations and measures to preserve participants’ confidentiality and anonymity

The project has been approved by the Clinical Research Ethics Committee. Moreover, in compliance with Spanish Law 15/1999 of 13th December on the Protection of Personal Data, authorization for dissemination of the results of the project will be sought from all participants, guaranteeing their anonymity and strict confidentiality. All participants’ names will be codified and assigned a number. The data obtained will be added to an archive named “MERTCEATE DATA” and the information provided by the questionnaires will be completely confidential. Any data or names that could be used to identify the participants will be eliminated. The data will be stored for the purposes of this research project. Participation among patients and health professionals will be voluntary and all participants will be required to provide their written informed consent indicating their acceptance of the study conditions and will retain the right to withdraw from the study at any point.

